**Fig. 2 Fig2:**
[figure not shown]
Potential Implementation Research Logic Model for RAPD (Rapid Adaptation to Prevent Drug use); an example set of strategies is listed in the “implementation strategies (RAPD)” box. MMH (Michigan Model for Health) curriculum is the evidence-based intervention being implemented

### Aim 2: design and pilot test RAPD deployment

#### Sample and setting

This pilot study, testing the set of implementation strategies designed based on Aim 1 results, will include ten middle schools from regions across the state (urban, rural, suburban) served by participating health coordinators. We anticipate 24 students per school, consistent with the mean number of students per classroom in Michigan [59]. The health coordinators’ service regions include one or more adjacent counties. We will enroll one or more health teachers from each participating school. Students aged 12–14 who are enrolled in the participating teacher’s classroom are eligible to participate in a pre- and post-implementation survey.

#### Sample size

Our proposed sample size includes 10 clusters with an average cluster size of 32 participants, consistent with the range reported in pilot cluster randomized controlled trials (inter-quartile range: 4–16 clusters; cluster size: 14–82) [60]. This sample size is appropriate for a pilot study designed to assess the feasibility and acceptability of implementing the intervention at the school level as primary and to estimate the variability in key implementation outcomes such as fidelity and student outcomes as secondary. This sample size also reflects the available resources for the pilot study while still allowing for meaningful data collection.

The justification for this sample size aligns with best practices for pilot studies, which prioritize achieving sufficient precision for key implementation parameters rather than powering analyses for statistical significance [52]. Given the exploratory nature of pilot studies, formal power calculations are not required, as the primary aim is to assess feasibility, variability, and implementation processes [61]. To ensure that our pilot sample will allow us to draw reasonable conclusions for the parameter estimates in a larger study, we conducted an AIPE (Accuracy in Parameter Estimation) analysis. We found that across 1000 simulations, the average 95% confidence interval widths for the student outcomes were 0.18 standardized units, and 0.85 for school-level variability. The focus on AIPE is more central to our aim in this pilot study than statistical power, especially for the school-level effects. Thus, our proposed sample size reflects a balance between the pragmatic constraints of a pilot trial and the need to collect adequate data to inform the design and conduct of subsequent larger-scale effectiveness trials.

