### Pilot study procedures

Per institutional IRB approval and to ensure ethical compliance, members of the study team and school health coordinators, including the study manager and Principal Investigator (PI), will disseminate study information to teachers, administrators, and parents at participating schools. Consistent with similar surveys in schools, we will provide parents with an opt-out option, and participant assent will be required before survey access. Students, then, will be allowed to participate in the study unless their parents explicitly choose to opt them out. Students will complete a self-administered survey with a unique identifier not linked to school or personal information. We will administer the survey through a secure online server to protect data confidentiality. As the MMH is incorporated into the school curriculum, students will complete the surveys during their health class before MMH delivery and upon course completion. For students without parental consent or those who choose not to assent, an alternative activity, such as a worksheet, will be provided to ensure their inclusion in school activities. Based on a 75% response rate, as observed in other community studies [88], we expect approximately 450 students to participate in the survey. As a study consistent with educational practices and existing school-based survey administration, there are few risks associated with participation; the primary adverse event of concern is potentially upsetting survey questions. Students who feel uncomfortable or upset by survey questions are permitted to skip questions or end participation at any time and are encouraged to report their concerns to their classroom teacher, which will then be shared with the study team. The researchers will report any adverse events to the institutional IRB.

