#### Student outcomes

Secondary outcomes at the student level are summarized in Table 2. Student surveys will be administered at baseline (the beginning of the semester or trimester), when the student is in health class, and after delivery of the drug use prevention units (post-test). During the school year, participating teachers will administer the pre-/post surveys for each cohort of students if they teach health for more than one term/year.

**Table 2 Tab2:** Secondary study measures student level

Student-level outcomes			
**Construct (# items)**	**Scaling**	**Timing**	**Source**

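### The protocol gives three student numbers that do not agree (240, 320 and about 450), and does not say which cluster size the precision simulation used

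*Protocol article*

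**What the plan says.** The number of schools is consistent: the pilot "will include ten middle schools from regions across the state". The number of students is not.

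- **Aim 2, Sample and setting:** "We anticipate 24 students per school, consistent with the mean number of students per classroom in Michigan". The same paragraph adds: "We will enroll one or more health teachers from each participating school".
- **Sample size:** the proposed sample is "10 clusters with an average cluster size of 32 participants". This section declines a formal power calculation and relies on an accuracy-in-parameter-estimation (AIPE) simulation, in which "the average 95% confidence interval widths for the student outcomes were 0.18 standardized units, and 0.85 for school-level variability".
- **Pilot study procedures:** "Based on a 75% response rate, as observed in other community studies", "we expect approximately 450 students to participate in the survey".
- **Student outcomes:** "participating teachers will administer the pre-/post surveys for each cohort of students if they teach health for more than one term/year".

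No section links the 24, the 32 and the 450. The Sample size section does not give the cluster size, intraclass correlation (ICC), pre/post correlation or target quantity of the simulation.

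**The concern.** These are three values for one planning quantity, the number of students expected in the survey, and they range from 240 to 450. This is not detail that an article leaves to a fuller document: the figures are all printed, and they conflict.

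Two things depend on the number. First, the AIPE simulation is the only quantitative justification of the sample size, and a reader needs to know which sample it describes. Second, the student data are meant to supply effect sizes, variances and power implications for a larger trial, so the planned student count is part of what the pilot promises.

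**Working it through.** **Inputs.** Ten schools and 24 students per school (Sample and setting); an average of 32 participants per cluster (Sample size); a 75% response rate and about 450 participants (Pilot study procedures); five schools per arm (Eligibility and randomization); AIPE width 0.18 for student outcomes (Sample size).

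**Step 1: try to reproduce 450.**

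| Source | Total | After 75% response |
|---|---|---|
| 10 x 24 | 240 | 180 |
| 10 x 32 | 320 | 240 |

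None of these is near 450. Working back, 450 / 0.75 = 600 approached. That is 600 / 10 = 60 approached and 450 / 10 = 45 responding per school. Against the other totals, 450 / 320 = 1.41 and 450 / 240 = 1.88.

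**Step 2: look for a reading that joins the figures.**

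- *32 approached, 24 responding.* Indeed 32 x 0.75 = 24. But the text calls the 32 participants and bases the 24 on mean class size, so the labels run the wrong way. The 450 also stays unexplained.
- *Several classes or cohorts per school.* Sixty approached per school is 60 / 24 = 2.5 classes of 24. More than one teacher or term could produce this, but no number of classes or terms is stated. The result, 45 respondents per school, still differs from an average cluster size of 32.

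**Step 3: ask whether the AIPE width reveals the sample size.** The article does not say what the 0.18 measures, so I tried two simple candidates, ignoring clustering, with z = 1.96.

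- One standardized mean, width = 2z / sqrt(N): 0.253 (N = 240), 0.219 (320), 0.185 (450). A width of 0.18 needs N = (2 x 1.96 / 0.18)^2, about 474.
- Pre/post change, width = 2z x sqrt(2(1 - r) / N), where r is the pre/post correlation (not given, so assumed). A width of 0.18 results when r = 0.75 (N = 240), 0.66 (320) or 0.53 (450).

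All three correlations are plausible, so 0.18 is compatible with each sample size and identifies none.

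**Step 4: size the effect on the between-arm comparison.** The arm difference is my choice of quantity. For five schools per arm and m students per school, the 95% interval width in SD units is 2 x 2.306 x sqrt(2 x (1 + (m - 1) x ICC) / (5m)), where 2.306 is the t value on 8 degrees of freedom. The ICC is an assumption, because the article gives none.

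| ICC (assumed) | m = 24 (N = 240) | m = 32 (N = 320) | m = 45 (N = 450) |
|---|---|---|---|
| 0.01 | 0.66 | 0.59 | 0.52 |
| 0.05 | 0.87 | 0.82 | 0.78 |
| 0.10 | 1.08 | 1.04 | 1.01 |

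For example, at ICC 0.05 and m = 24: 4.612 x sqrt(2 x 2.15 / 120) = 0.87. From 240 to 450 students the width falls by about 11% at ICC 0.05, by 21% at 0.01 and by 7% at 0.10. Treating students as independent, 4z / sqrt(N) gives 0.51, 0.44 and 0.37, but that does not fit a trial randomized by school.

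**The case against.** The best defence is that the Sample size section hangs together. It opens with ten clusters averaging 32, defends that sample, and reports the AIPE result for the pilot sample, so the natural reading is 10 x 32. This stands. A reader might infer that the basis of the precision analysis is wholly undetermined, but that goes too far. What is true is narrower: the simulated cluster size is not stated and cannot be recovered from the width.

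Three other inferences are tempting and are not supported.

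- *That the student analysis needs complete pre/post pairs, so the 75% should be applied twice.* The Student data section plans mixed models with random intercepts, and the Missing data section names multiple imputation and full information maximum likelihood. These can use students with a single survey, and some student outcomes are measured only after implementation.
- *That the progression rule is compromised because a school could be on target under one figure and short under another.* The traffic-light text under Mixed method data integration gives no numeric target, and nothing ties it to 240, 320 or 450.
- *That expected respondents could be as few as 180.* This comes from applying 75% to 24 per school, which the article nowhere does.

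It is also fair to say that the primary outcomes come from teacher interviews and a teacher survey, that student outcomes are secondary and exploratory, and that the article provides for more than one teacher and cohort per school. The last point makes a larger total possible, but it does not bring 45 respondents per school into line with 32.

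**Conclusion.** The inconsistency is real: 240, 320 and about 450 cannot all describe the expected student sample, and no stated assumption connects them. It follows from the printed figures by multiplication alone.

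Its reach is modest. It affects the secondary student outcomes and the precision justification, and leaves the number of schools and the primary analysis untouched. Because the number of schools dominates between-arm precision, the choice among the three totals moves the arm-difference width only from about 0.87 to 0.78 SD. That figure assumes an ICC of 0.05, equal cluster sizes and 8 degrees of freedom; a smaller ICC would make the difference larger. The point should be corrected, but it ranks below a must-fix.

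**What to change.** Use one chain in Sample and setting, Sample size and Pilot study procedures: students approached per school (students per class x classes x terms), times the 75% response rate, giving expected participants per school and in total. Say explicitly whether 24, 32 and 45 are class sizes, students approached or respondents, and drop any figure that does not fit the chain.

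State the cluster size used in the AIPE simulation. If it differs from the reconciled figure, rerun the simulation and restate the 0.18 and 0.85.

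The cost is a few sentences and at most one rerun. The reported widths may change, and could become less favourable if the reconciled sample is smaller than the one simulated.

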#### Eligibility and randomization

We will focus on schools that could most benefit from RAPD by employing the following screening criteria: schools must include seventh-grade education level; health teachers must report delivering less than 80% of the MMH curriculum (the state-identified fidelity standard) and/or report two or more barriers to MMH implementation (see “Measures”). These criteria are adapted from a previous school-based study and informed by study partners and the study team's previous research on MMH implementation [62, 63]. Five of the matched sites will be randomized to the RAPD and five to standard implementation: the MMH curriculum manual, training, and technical assistance. Research team members will use the GenRandGroups function within the DescTools package (version 0.99.54) in R. The randomization procedure is designed to pilot methods to ensure balanced participant allocation across experimental conditions. Schools will be the randomization unit, with matching criteria for assigning schools to treatment groups involving factors such as school size, the percentage of students eligible for free/reduced lunch, and the health coordinator serving the school. Participants (schools) were not masked as is not practical or desired in this implementation study, which focuses on improving the speed, quality, and quantity of intervention delivery through different strategies, acknowledging the influence of participants' awareness on observable outcomes. The health coordinators have successfully recruited schools for previous similar studies [63, 64]. All standard implementation sites will receive RAPD following the trial portion of the study. We focus on middle school because of the heightened risk for drug use initiation during this developmental period [65].

### Procedures

#### RAPD implementation strategy design

We will use the Implementation Research Logic Model (IRLM) to organize and synthesize the gaps identified in Aim 1 into actionable implementation strategies to address these gaps. This process will support the rigor and reproducibility of this research for broad application when engaging in rapid responses. While the findings from Aim 1 will ultimately shape the implementation strategy specification for the pilot trial, collectively referred to as RAPD, we provide an example of anticipated key determinants (i.e., gaps; see Fig. 2) based on our previous and preliminary research [20, 66], existing research [19, 67], and other work focused on Tier 1 substance use prevention [63, 68]. Our logic model specifies determinant relationships with implementation strategies, mechanisms of action, and anticipated outcomes [58]. We will use the Consolidated Framework for Implementation Research (CFIR) to identify and organize the “gaps” to be targeted for implementation strategies. CFIR is a comprehensive determinant framework that includes domains across socioecological levels (e.g., intervention, inner and outer context, provider characteristics) and whose overarching aim is to understand and identify central factors, that is, gaps and best practices, that influence intervention delivery in a given setting [69, 70].

As implementation is inherently complex, researchers and practitioners are challenged to identify the consistent impact of implementation strategies to mitigate barriers to effective intervention delivery [71]. Systematic processes for matching gaps and implementation strategies and assessing their proposed mechanisms of action are needed. Implementation science researchers have created tools, such as the Consolidated Framework for Implementation Research (CFIR)-implementation strategy matching tool online to support researchers and practitioners in selecting suitable strategies [72]. We will use the SISTER: School Implementation Strategies Translating ERIC (Expert Recommendations for Implementing Change) Resources taxonomy to specify implementation strategies [56]. We will also consider and assess possible mechanisms of action, that is, processes through which implementation strategies operate to influence outcomes [73]. Examples of possible strategies include promoting intervention adaptability, providing ongoing training, and implementation facilitation.

#### Promoting EBI adaptability

To promote adaptability in drug use prevention programs, we will use fidelity-consistent adaptations that meet the population's specific needs (e.g., new drugs) while preserving the core elements of evidence-based interventions [74]. The interventions' core functions align with their intended outcomes and purpose [73]. For instance, we systematically incorporate up-to-date drug use prevention information, like the vaping example from Aim 1, while maintaining the essential components of the intervention (MMH core functions). Thus, we will collaborate with state agencies and community partners to facilitate these updates and enhance adaptability. We will share information from ongoing drug use-related efforts and swiftly integrate available options, information, and resources into the MMH-the form elements. Form elements can be tailored to the setting [75]. We will provide briefs on new policies, expert preliminary guidelines, and supplementary resources for the curriculum and families.

Recognizing the diverse needs of schools, especially those serving economically disadvantaged and marginalized students, we will offer tailored options for curriculum adaptation. These include information sensitive to families at higher risk of substance use disorders or adversity and activities with additional support and evaluation to foster skill development. This flexible and targeted approach enables us to address emergent drug use issues that complement the existing MMH curriculum.

#### Ongoing training

Researchers have found that the uptake, fidelity, and sustainment of EBIs can be markedly improved by providing ongoing training; this is especially useful when tailored to the local needs and context, including the unique needs of low-resource environments [75]. Training is a valuable strategy that can be used to adopt and sustain innovations effectively [76]. Teachers faced with providing content outside their expertise, as with new drugs, may be less likely to deliver the content with fidelity, if at all [77, 78]. Training can improve behavioral capability by building knowledge, skills, and self-efficacy; this will build mastery for new content delivery, improving fidelity [71, 79]. Health coordinators are well suited to providing ongoing teacher training as this is within their current scope of practice. Training can also promote implementation and sustainment by enhancing staff’s EBI enthusiasm, vital to promoting intervention fidelity [77, 78, 80].

#### Implementation facilitation

 Is a crucial aspect of successful implementation, supported by research indicating that having a community-based expert and support person, such as a school health coordinator, significantly increases the likelihood of positive outcomes [76]. In the context of our intervention, facilitation serves as a flexible strategy tailored to address barriers related to the intervention, context, recipients (students), or providers. Based on the integrated Promoting Action on Research Implementation in Health Services (iPARIHS) framework, facilitation involves providing individualized assistance for intervention delivery [81]. This approach includes interactive problem-solving and ongoing collaboration to overcome barriers tailored to the provider and contextual needs. Tailored support is vital to effectively reach underserved populations, including organizations serving youth at higher risk of substance use disorders, and to achieve desired public health outcomes [82]. Although facilitation has predominantly been deployed in clinical settings [83, 84], preliminary evidence from a recent, large-scale, school-based implementation study suggests that facilitation also positively impacts school EBI adoption [85]. Therefore, facilitation will likely enhance the acceptability of our MMH program and boost teacher self-efficacy in delivering the intervention.

### Study design

The pilot study will use a mixed method, hybrid effectiveness-implementation, 2-group cluster-randomized trial (CRT) design to investigate deploying RAPD for delivering MMH (Fig. 3). Specifically, the study uses a hybrid type 2 approach, which includes evaluating potential implementation strategy effects on provider practices and exploring participant outcomes [86, 87]. Standard implementation consists of the MMH digital curriculum, standard MMH training, and as-needed technical assistance from the health coordinators. RAPD will augment standard implementation with additional strategies based on Aim 1 results. See Fig. 2 for possible RAPD strategies and Fig. 3 for pilot study design.

**Fig. 3 Fig3:**
[figure not shown]
Aim 2 study design

### Pilot study procedures

Per institutional IRB approval and to ensure ethical compliance, members of the study team and school health coordinators, including the study manager and Principal Investigator (PI), will disseminate study information to teachers, administrators, and parents at participating schools. Consistent with similar surveys in schools, we will provide parents with an opt-out option, and participant assent will be required before survey access. Students, then, will be allowed to participate in the study unless their parents explicitly choose to opt them out. Students will complete a self-administered survey with a unique identifier not linked to school or personal information. We will administer the survey through a secure online server to protect data confidentiality. As the MMH is incorporated into the school curriculum, students will complete the surveys during their health class before MMH delivery and upon course completion. For students without parental consent or those who choose not to assent, an alternative activity, such as a worksheet, will be provided to ensure their inclusion in school activities. Based on a 75% response rate, as observed in other community studies [88], we expect approximately 450 students to participate in the survey. As a study consistent with educational practices and existing school-based survey administration, there are few risks associated with participation; the primary adverse event of concern is potentially upsetting survey questions. Students who feel uncomfortable or upset by survey questions are permitted to skip questions or end participation at any time and are encouraged to report their concerns to their classroom teacher, which will then be shared with the study team. The researchers will report any adverse events to the institutional IRB.

